#### **8.4 Patient Management of Adverse Events**

All AEs will be treated as clinically indicated and concomitant treatment recorded on the Concomitant Medication CRF. If necessary, participants will be referred for specialist care.

The research team will treat and pay for minor AEs or any AE that requires hospital management that is clearly related to the study drug/s e.g. haemolysis requiring a blood transfusion.

All patients will be followed up until the AE resolved or stabilised even if this occurs past study D42. This includes patients who withdraw themselves or have been withdrawn from the study by the PI.

#### **8.5 Serious Adverse Events**

In this study, an AE is a serious AE if it results in any of the following outcomes:

- Death
- Life-threatening event – this means that the patient was at immediate risk of death at the time of the event and required immediate medical intervention. It does not refer to an event which hypothetically might have caused death if it were more severe.
- Prolongation of existing hospitalisation or re-hospitalisation once discharged.
- Persistent or significant disability/incapacity
- An important medical event that may not be immediately life-threatening or result in death or hospitalization but may jeopardize the patient or may require intervention to prevent one of the other outcomes listed in the definition above.

All SAEs will be recorded on the SAE CRF.

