### **3.10.6 Admission to hospital**

At the KIMORU research centre in Kinshasa, study patients are routinely admitted for at least three days or longer according to their clinical course.

In Uganda, all caretakers/guardians will be invited to allow their child to be admitted to hospital for at least 48 hours for close monitoring and to receive directly observed therapy for all doses of their treatment. Children of caretakers/guardians who decline this invitation will be followed up as outpatients; this will include daily visits to the hospital so as to record clinical observations and monitor their treatment.

This decision has been taken mostly because caretakers/guardians prefer their children to be admitted.

Hb data will be continue to be sent weekly to the Data Monitoring and Ethics Committee (DMEC) by both sites.

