#### **8.6 Expedited Reporting of Serious Adverse Events**

Expedited reporting means the rapid reporting of SAEs.

All SAEs, irrespective of their relationship to the study drugs, will be reported within 24 hours to:

- the study PI, [name]: [[contact]](mailto:[contact])
- the coPI/study coordinator - [name]: [[contact]](mailto:[contact])
- the MORU pharmacovigilance officer

This initial contact can be a brief email or fax ([contact]) to alert the team of a SAE. Thereafter, a SAE form will be completed. Follow up SAE reports will be sent as needed.

The study coordinator will then alert the DMEC.

The research teams will be responsible for reporting SAEs to any local regulatory or ethical body, if this is required.

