### **9 DATA MONITORING & ETHICS COMMITTEE**

An independent DMEC will be established and consist of qualified volunteers with the necessary knowledge of clinical trials and G6PD deficiency. There will also be a statistician.

A DMEC charter will be written that will be reviewed and approved by the DMEC. The charter will outline the DMEC responsibilities, frequency of meetings, and, notably, details of safety monitoring and which data the DMEC wishes to see in real time. The DMEC will review all data in the strictest confidence. Data that the DMEC will review will include:

- Hb data in the first 50 RDT diagnosed G6PDd patients in real time
- Hb data in the first 100 children admitted in Uganda to review the admissions policy
- all SAEs irrespective of the causality to study drugs
- AEs every 6 months.

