**18 APPENDIX 2: STUDY SCHEDULE – UGANDA OUTPATIENTS**

| Initial patient management  |   |  |  |  |  |  |  |  |  |  |  |  |  |  | Blood volumes |       |
|-----------------------------|---|--|--|--|--|--|--|--|--|--|--|--|--|--|---------------|-------|
| Verbal consent              | X |  |  |  |  |  |  |  |  |  |  |  |  |  |               | total |
| Brief history & examination | X |  |  |  |  |  |  |  |  |  |  |  |  |  |               |       |
| Hb (HemoCue)                | X |  |  |  |  |  |  |  |  |  |  |  |  |  | 0.02          | 0.02  |
| Malaria RDT                 | X |  |  |  |  |  |  |  |  |  |  |  |  |  | 0.02          | 0.02  |
| G6PD RDT qualitative        | X |  |  |  |  |  |  |  |  |  |  |  |  |  | 0.02          | 0.02  |
|                             |   |  |  |  |  |  |  |  |  |  |  |  |  |  |               |       |
|                             |   |  |  |  |  |  |  |  |  |  |  |  |  |  |               |       |
|                             |   |  |  |  |  |  |  |  |  |  |  |  |  |  |               |       |
|                             |   |  |  |  |  |  |  |  |  |  |  |  |  |  |               |       |
|                             |   |  |  |  |  |  |  |  |  |  |  |  |  |  |               |       |
|                             |   |  |  |  |  |  |  |  |  |  |  |  |  |  |               |       |
|                             |   |  |  |  |  |  |  |  |  |  |  |  |  |  |               |       |
|                             |   |  |  |  |  |  |  |  |  |  |  |  |  |  |               |       |
|                             |   |  |  |  |  |  |  |  |  |  |  |  |  |  |               |       |
|                             |   |  |  |  |  |  |  |  |  |  |  |  |  |  |               |       |
|                             |   |  |  |  |  |  |  |  |  |  |  |  |  |  |               |       |
|                             |   |  |  |  |  |  |  |  |  |  |  |  |  |  |               |       |
|                             |   |  |  |  |  |  |  |  |  |  |  |  |  |  |               |       |
|                             |   |  |  |  |  |  |  |  |  |  |  |  |  |  |               |       |
|                             |   |  |  |  |  |  |  |  |  |  |  |  |  |  |               |       |
|                             |   |  |  |  |  |  |  |  |  |  |  |  |  |  |               |       |
|                             |   |  |  |  |  |  |  |  |  |  |  |  |  |  |               |       |

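### The hospitalisation criterion for SAEs omits a first admission, so an adverse event that first brings a Ugandan outpatient into hospital is not automatically serious

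*Protocol*

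**What the plan says.** Section 8.5 of the protocol lists five outcomes that make an adverse event serious: death, a life-threatening event, a hospitalisation criterion, disability, and an important medical event. The hospitalisation criterion reads "Prolongation of existing hospitalisation or re-hospitalisation once discharged".

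Section 3.10.6 sets out who is admitted. In Kinshasa, "study patients are routinely admitted for at least three days or longer according to their clinical course". In Uganda, admission for at least 48 hours is offered to all, but "Children of caretakers/guardians who decline this invitation will be followed up as outpatients", with daily hospital visits. This is a planned pathway with its own appendix, headed "STUDY SCHEDULE – UGANDA OUTPATIENTS".

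Section 8.6 ties prompt reporting to SAE status: "All SAEs, irrespective of their relationship to the study drugs, will be reported within 24 hours to" the study's lead investigator, the coordinator and the pharmacovigilance officer, after which the coordinator alerts the DMEC. Section 9 lists what the DMEC reviews, including "all SAEs irrespective of the causality to study drugs" and, separately, AEs at six-month intervals.

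**The concern.** The criterion is written as if every child starts the trial in a hospital bed. That fits Kinshasa and the admitted Ugandan children. It does not fit a Ugandan child whose caretaker declined admission: when an adverse event first brings that child into hospital, neither limb is met.

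The trial's primary question is safety, and the seriousness label decides whether the 24-hour route is used. As written, the label can depend on the caretaker's choice about admission at enrolment as well as on what happened to the child. At stake are the speed with which the DMEC learns of such admissions and a consistent meaning of SAE across the two care settings.

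**Working it through.** No arithmetic applies. The check takes an adverse event that requires hospital care and follows it through the protocol's rules for three kinds of child.

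**Step 1: is the hospitalisation criterion (section 8.5) met?**

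| Child's status when the event occurs | Existing stay? | Earlier study discharge? | Criterion met? |
|---|---|---|---|
| Inpatient (Kinshasa, or Uganda admitted), event extends the stay | yes | not needed | yes, as prolongation |
| Discharged after the study admission, event leads to readmission | no | yes | yes, as re-hospitalisation |
| Ugandan outpatient since enrolment, event leads to first admission | no | no | **no** |

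An inpatient's event that is dealt with inside the planned stay is not automatically serious either. The contrast is between events that lengthen or renew a stay and events that start one.

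**Step 2: do the other four criteria catch the third row?**

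- Death and disability apply only if those outcomes occur.
- The life-threatening criterion requires that "the patient was at immediate risk of death at the time of the event and required immediate medical intervention". An admission short of that does not qualify.
- The important-medical-event criterion can apply, but by judgement. It is meant for events that "may not be immediately life-threatening or result in death or hospitalization but may jeopardize the patient", or that may need intervention to prevent an outcome listed earlier. That wording treats hospitalisation in general as already on the list. A first hospitalisation is not on it, so the definition is inconsistent within itself.

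**Step 3: what follows if none of the five applies?**

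- The 24-hour report (sections 8.3 and 8.6) is not triggered, and neither is the DMEC alert, which follows from it.
- The event is still recorded, because section 8.3 requires AEs of every severity on the AE/SAE form.
- The DMEC sees it in the six-monthly AE review (section 9).
- A fall in haemoglobin also appears in the weekly Hb data sent by both sites (section 3.10.6), and in real time if the child is among the first 50 RDT-diagnosed G6PD-deficient patients (section 9). An Hb value does not tell the DMEC that the child was admitted, and admissions for other reasons leave no trace in that feed.

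**Step 4: is the treatment comparison touched?** Randomisation lists are separate by site and G6PD group (section 3.10), and primaquine/placebo is double blind (section 3.2). The same wording applies to both arms. The primary endpoint (section 3.3) is defined by haemoglobin and severity features, not by SAE status.

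**The case against.** The strongest reply is that this is loose drafting with little practical effect. The important-medical-event criterion speaks of hospitalisation as though it were already a serious outcome, so an investigator could readily class a first admission as an SAE. An admission for a marked fall in haemoglobin would plausibly qualify under that criterion anyway, as might repeated vomiting that leads to parenteral rescue. The outpatients are seen daily during treatment. All AEs are recorded, the DMEC reviews them, it receives Hb data weekly, and its charter may ask for more in real time.

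Most of this stands and limits the consequence. It does not close the gap. The life-threatening criterion is narrow and the important-event criterion is discretionary, whereas a hospitalisation criterion exists so that reporting an admission does not rest on case-by-case judgement. Recording an event for a six-monthly review is also not the same as reporting it within 24 hours.

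Two stronger readings are tempting, and the protocol supports neither. A reader might infer that these admissions would never reach the DMEC; sections 3.10.6, 8.3 and 9 show that they would, only later or in part. A reader might also infer that the SAE comparison between primaquine and placebo is biased. The rule is the same in both blinded arms, and the protocol plans no comparison of SAE rates between inpatients and outpatients or between sites.

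**Conclusion.** The gap in wording is certain: sections 8.5 and 3.10.6 do not fit together, and the fifth criterion of section 8.5 presumes an item that the list lacks. A first AE-related admission of a Ugandan outpatient is not automatically an SAE. Unless another criterion is met, the 24-hour report and the prompt DMEC alert are missed.

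The size cannot be estimated. The protocol gives neither the Ugandan share of the 1600 patients (section 11.1 allows up to 1200 at either site) nor the proportion of caretakers who decline admission. A reader might assume 800 Ugandan children with 10% to 50% as outpatients, and arrive at 0.10 × 800 = 80 to 0.50 × 800 = 400 children. Those inputs are not in the protocol, and the result counts children on the pathway, not events missed. The relevant number is the subset who have a first admission for an AE that meets no other criterion. It is probably small, since section 3.10.6 says caretakers prefer admission and the other criteria will catch many of the graver events.

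The harm is to timely and uniform safety reporting. The primary endpoint and the between-arm comparison are unaffected.

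**What to change.** Reconcile section 8.5 with section 3.10.6. Put a new limb at the front of the hospitalisation criterion, keeping the two existing limbs: hospital admission for an adverse event, other than the planned study admission at enrolment. Tying it to an adverse event keeps out the child whose caretaker simply accepts the invitation later. The fifth criterion's reference to hospitalisation then agrees with the list. Amend the SAE form to match.

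The cost is one line in the protocol, one on the form, and a few more SAE reports. It is a reporting rule only and changes nothing in how children are treated.

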#### **8.6 Expedited Reporting of Serious Adverse Events**

Expedited reporting means the rapid reporting of SAEs.

All SAEs, irrespective of their relationship to the study drugs, will be reported within 24 hours to:

- the study PI, [name]: [[contact]](mailto:[contact])
- the coPI/study coordinator - [name]: [[contact]](mailto:[contact])
- the MORU pharmacovigilance officer

This initial contact can be a brief email or fax ([contact]) to alert the team of a SAE. Thereafter, a SAE form will be completed. Follow up SAE reports will be sent as needed.

The study coordinator will then alert the DMEC.

The research teams will be responsible for reporting SAEs to any local regulatory or ethical body, if this is required.

### **9 DATA MONITORING & ETHICS COMMITTEE**

An independent DMEC will be established and consist of qualified volunteers with the necessary knowledge of clinical trials and G6PD deficiency. There will also be a statistician.

A DMEC charter will be written that will be reviewed and approved by the DMEC. The charter will outline the DMEC responsibilities, frequency of meetings, and, notably, details of safety monitoring and which data the DMEC wishes to see in real time. The DMEC will review all data in the strictest confidence. Data that the DMEC will review will include:

- Hb data in the first 50 RDT diagnosed G6PDd patients in real time
- Hb data in the first 100 children admitted in Uganda to review the admissions policy
- all SAEs irrespective of the causality to study drugs
- AEs every 6 months.

## 10 MANAGEMENT OF SEVERE / PROFOUND ANAEMIA

### 10.1 General principles

In malaria, the Hb tends to fall initially before recovering. Anaemic African children with high parasite counts are prone to developing profound and severe anaemia that may require rescue with a blood transfusion. Detailed guidelines will be written on anaemia management and will be included in prestudy training.

### 10.2 Indications for blood transfusion include:

Children often tolerate lower Hb concentrations than adults, so their Hb thresholds for triggering a blood transfusion are generally lower.

The indications for transfusion are:

- Hb < 4 g/dL , irrespective of the clinical condition of the patient
- Hb < 5g/dL, if any of the following clinical features are present:
  - respiratory distress encompassing:
    - dyspnoea at rest
    - tachypnoea and
    - deep respirations
  - dyspnoea on mild exertion
  - acidosis (usually manifests as respiratory distress).
  - impaired consciousness
  - prostration

## 11 STATISTICS

### 11.1 Sample size

The sample size is based on demonstrating non-inferiority of ACT + SLDPQ compared to ACT alone with respect to the development of profound/severe anaemia in the G6PDd group. The rate of profound/severe anaemia in AL treated uncomplicated *P. falciparum* in Kinshasa is 1.5%.

For a non-inferiority margin of 2.5%, a two sided alpha=0.05 and a power of 80%, the sample size per group is 374 patients. Allowing for a 5% loss to follow up this become 393. We will recruit 800 G6PDd patients, the majority of whom will be males.

We will also recruit 800 patients into the G6PD normal arm, for a total sample size of 1600 patients. In the G6PD normal group, we expect the male-female ratio to be close to 1 and the age distribution to be very similar to that of the G6PDd group. The majority of malaria patients will be < 5 years old.

We plan to recruit a total of 1600 patients across both sites. Local ethical approval will be sought to recruit up to 1200 patients per site in case one of the sites experiences difficulties in recruitment.

Although genetic studies have shown relative high G6PDd allele frequencies, we are mindful of the weak correlation between G6PD genotypes and enzyme activities. Therefore, we have assumed a 10% proportion of G6PD RDT diagnosed G6PDd patients (most will be male) to calculate the number of patients we will need to screen ~8500 patients to obtain 800 G6PDd patients.

For other IBDs, we expect to recruit ~596 thalassaemia heterozygotes (prevalence 37.5%), ~246 sickle cell trait (15.7%), ~103 thalassaemia homozygotes (6.6%), and 14 sickle cell disease patients (0.9%).

## 11.2 Analyses & analysis populations

All patients who received at least one dose of ACT and PQ/placebo will be included in the analysis. All analyses will be detailed later in a prospectively written analysis plan. Below is a summary.

The main strategy for analysis of the primary end point will be assessed by chi squared or Fisher's exact test, as appropriate, calculating the 95% CIs of the risk difference to see if ACT + SLDPQ has achieved non-inferiority in the G6PDd group. Logistic regression will be used to adjust for potential confounders. Non inferiority will be assessed on the whole data set i.e. combining data from both sites using the lower end of the 95% confidence interval. Other proportional data will also be analysed by chi squared or Fisher's exact test.

Continuous data (e.g. Hb, biochemistry, parasite counts) between two groups will be analysed by the unpaired 't' test, transforming the data, as needed.

All analyses will be two sided and a p value of < 0.05 is considered statistically significant.

We will examine factors that are associated with: (i) the development of profound / severe anaemia (logistic regression), (ii) parameters of Hb recovery (multiple regression). *A priori*, we will explore the relationships between Hb profiles in the following: (i) G6PD status (defined by genotype and by enzyme activity), (ii) any IBD vs. not, (iii) age <5 vs. age ≥5y, (iv) high biomass infections, assessed by microscopy and measured HRP2 concentrations, and (v) males vs. females. For these analyses, estimates and 95% confidence intervals (CIs) will be presented but not p values.

The PK data for PQ and cPQ will be analysed by non-compartmental analysis. The following PK parameters will be estimated:

- Cmax
- Tmax
- Clearance
- Half life
- AUC
- Vd

For lumefantrine and piperaquine, drug absorption kinetics will be modelled over the first 24 hours.

The Day 7 concentrations of lumefantrine and piperaquine will be compared between PQ and placebo recipients. Depending on the lumefantrine and piperaquine data obtained, other modelled PK parameters will be determined, as the data permit.

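### Section 11.2 should let the risk-difference interval alone decide non-inferiority, state its direction (the upper limit for SLDPQ minus placebo), and put the adjusted result on the same scale

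*Protocol*

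**What the plan says.** Protocol section 11.1: "The sample size is based on demonstrating non-inferiority of ACT + SLDPQ compared to ACT alone" for profound or severe anaemia in the G6PD-deficient (G6PDd) group. The reference rate "in Kinshasa is 1.5"%, and the calculation reads: "For a non-inferiority margin of 2.5%, a two sided alpha=0.05 and a power of 80%, the sample size per group is 374 patients".

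Protocol section 11.2 opens the primary analysis with "The main strategy for analysis of the primary end point will be assessed by chi squared or Fisher's exact test, as appropriate". The sentence then continues: 95% CIs of the risk difference will be calculated to see whether ACT + SLDPQ is non-inferior in the G6PDd group. Next comes "Logistic regression will be used to adjust for potential confounders". A further sentence says that non-inferiority is judged on both sites combined, from the lower limit of the 95% CI. A general rule follows: "All analyses will be two sided and a p value of < 0.05 is considered statistically significant".

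The section describes itself as a summary and leaves detail to a later analysis plan. It does not say which arm is subtracted from which, or what part the chi-squared or Fisher p value plays beside the interval.

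**The concern.** The hypothesis to be rejected is that SLDPQ raises the risk of profound or severe anaemia by 2.5 points or more. A chi-squared or Fisher test has equal risk as its null. A logistic coefficient is ordinarily tested against an odds ratio of 1. Neither says whether an excess of 2.5 points has been excluded, so a non-significant p value could be taken as reassurance on a safety endpoint when it is not.

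The interval does address the margin, but only at the correct end. The outcome is a harm. If the difference is SLDPQ minus placebo, the limit that must clear the margin is the upper one, against +2.5 points. The lower limit is right only for placebo minus SLDPQ, against -2.5 points. With the direction unstated, the sentence can be carried out in a way that reverses its meaning.

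The crude result is a risk difference and the adjusted result would be an odds ratio. The second could then neither support nor weaken the first against the margin.

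**Working it through.** **Inputs.** From section 11.1: control risk 1.5%, margin 2.5 points, two-sided alpha 0.05 (one-sided 0.025 for non-inferiority), power 80%, 374 per group, 800 G6PDd patients, 5% loss. Assumed: 1:1 allocation to SLDPQ and placebo (the allocation figure is not shown), so 400 per arm, or 380 after 5% loss; and 1.5% in both arms when SLDPQ has no effect.

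**1. The plan's own sample size.** n = (z₀.₉₇₅ + z₀.₈₀)² × 2p(1-p) / margin² = (1.960 + 0.842)² × 2 × 0.015 × 0.985 / 0.025² = 371.1, so 372, against the stated 374. Loss to follow-up: 374 × 1.05 = 392.7, so 393 as stated. A design to detect 1.5% versus 4.0% with an equality test would need 671 per group. The trial is therefore sized for an interval against the margin, not for chi-squared or Fisher.

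**2. Equality test against interval.** Take 10 versus 6 events at 380 per arm.
- Difference: 10/380 - 6/380 = 2.63% - 1.58% = 1.05 points.
- Standard error: √(0.0263 × 0.9737/380 + 0.0158 × 0.9842/380) = 0.0104.
- Wald 95% CI: 1.05 ± 1.96 × 1.04 = -0.99 to +3.09 points.
- Chi-squared p = 0.31; Fisher p = 0.45.

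The arms do not differ significantly, yet an excess of 2.5 points is not excluded.

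**3. Which end of the interval.** The same table read three ways:
- SLDPQ minus placebo, upper limit +3.09 against +2.5: not shown.
- Placebo minus SLDPQ, lower limit -3.09 against -2.5: not shown (the same decision).
- SLDPQ minus placebo, lower limit -0.99 against -2.5: met.

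Over 400,000 simulated trials at 380 per arm (Wald interval, uncorrected chi-squared):

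| True risks, SLDPQ vs placebo | Upper limit < +2.5 | Lower limit > -2.5 | Chi-squared not significant |
|---|---|---|---|
| 1.5% vs 1.5% | 81.4% | 81.4% | 95.8% |
| 4.0% vs 1.5% (at the margin) | 3.6% | 99.3% | 43.0% |

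Both limit columns are for SLDPQ minus placebo. With no true effect the two readings perform alike, so the error would not show up in a power check. It shows only when SLDPQ is harmful.

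**4. Odds ratio against the margin.** The odds ratio equal to a 2.5-point excess is [(p + 0.025)/(1 - p - 0.025)] / [p/(1 - p)].
- p = 1.5%: (0.040/0.960)/(0.015/0.985) = 2.74.
- p = 0.5% (assumed): (0.030/0.970)/(0.005/0.995) = 6.15.
- p = 3% (assumed): (0.055/0.945)/(0.030/0.970) = 1.88.

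No single odds-ratio limit stands in for 2.5 points.

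**5. Choice of interval.** Exact enumeration of all event pairs, non-inferiority declared when the upper limit is below +2.5 points:

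| | Wald | Score |
|---|---|---|
| 1.5% both arms, 374 per arm | 79.8% | 69.0% |
| 1.5% both arms, 400 per arm | 81.5% | 74.1% |
| 4.0% vs 1.5%, 374 per arm | 3.4% | 2.2% |

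The nominal error is 2.5%. Expected events are few: 800 × 0.015 = 12 in the whole G6PDd group.

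**The case against.** A reader might infer from the named tests that the non-inferiority hypothesis is left untested. The document does not support that. The sentence goes on past the tests to the 95% CI of the risk difference and ties the purpose of judging non-inferiority to that interval. A later sentence again assesses non-inferiority from the interval. Comparing it with 2.5 points is a valid test on the scale of the margin. It also follows that non-significance at an unacceptable excess (43.0% of trials by chi-squared) is not the error rate of the plan, because the plan does not decide by that p value. In the 10 versus 6 example the interval, read at the correct end, gives the right answer.

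A second tempting reading is that the plan has fixed a reversed rule. That is not established either, since placebo minus SLDPQ would make the lower limit correct. Section 11.1 names ACT + SLDPQ first in the comparison, which invites the opposite subtraction but does not settle it.

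Third, logistic regression is offered only to adjust for confounders and no adjusted non-inferiority decision is claimed. The interval method and model fitting belong in the analysis plan.

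All of this stands. What it leaves is a section that sets an equality test beside the interval without ranking them, applies a p < 0.05 rule to all analyses, cites one limit without a direction, and names an adjusted analysis that cannot be read against the margin. These are things the protocol states, not details it defers.

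**Conclusion.** The point holds as a fault of specification in section 11.2, not of design. The sample size reproduces to within 2 patients and already fits an interval against 2.5 points.

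The largest exposure is the direction. Under the wrong pairing (SLDPQ minus placebo, lower limit, -2.5 points), non-inferiority would be declared in about 99% of trials at a true 4.0% versus 1.5%, instead of about 4%. This is what the wording permits, not what the sponsor is shown to intend. The equality p value carries a smaller risk, of misinterpretation only. The odds-ratio mismatch limits the use of the adjusted result but does not touch the primary decision.

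The figures rest on 1:1 allocation, 1.5% control risk and, in the simulation, 380 per arm with a Wald interval.

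**What to change.** In section 11.2:
- State that non-inferiority is decided solely by whether the upper limit of the two-sided 95% CI for the risk difference, SLDPQ minus placebo, in the G6PDd group with both sites combined, is below +2.5 percentage points. Remove the reference to the lower limit.
- State that the chi-squared or Fisher p value for the primary endpoint is descriptive and plays no part in that conclusion, and exempt the primary endpoint from the general p < 0.05 rule. Keep these tests for the other proportions.
- Report the covariate-adjusted result as a standardised (marginal) risk difference from the logistic model, with its 95% CI, against the same 2.5-point margin.

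The interval method and any penalised fit can be left to the analysis plan, but should be fixed before unblinding with the trade-off in view. With about 12 expected events, a score interval controls error better at the margin (2.2% against 3.4%) but has power of 69 to 74%, against about 80% for Wald.

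The cost is a few sentences and a little code. The sample size does not change, and no extra patients or data are needed. The loss of power arises only if the score interval is chosen.

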#### 3.3 Primary Endpoint

The primary outcome is the proportion of patients who, within the first 21 days, develop either:

- profound anaemia [Hb concentration < 4g/dL] or
- severe anaemia (Hb <5g/dL) with severity features e.g. impaired consciousness or deep breathing.

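### Section 11.2 judges non-inferiority on the lower confidence limit for a harmful outcome without defining the direction of the difference; under the usual convention that limit cannot rule out excess harm

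*Protocol*

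**What the plan says.** Section 3.3 defines an adverse outcome. It counts children who reach one of two states of anaemia ("The primary outcome is the proportion of patients who, within the first 21 days, develop either"): Hb under 4 g/dL, or Hb under 5 g/dL accompanied by features of severity. A higher proportion is worse.

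Section 11.1 sizes the trial for "demonstrating non-inferiority of ACT + SLDPQ compared to ACT alone with respect to the development of profound/severe anaemia in the G6PDd group". It takes a 1.5% event rate from AL-treated children in Kinshasa and gives the margin without a sign ("For a non-inferiority margin of 2.5" per cent). With two-sided alpha 0.05 and 80% power it arrives at 374 per group, 393 after allowance for loss to follow-up, and a recruitment target of 800 G6PDd children.

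Section 11.2 makes the 95% CI of the risk difference the basis for the non-inferiority conclusion in the G6PDd group. It then names the limit that decides: the assessment is made by "combining data from both sites using the lower end of the 95% confidence interval". No section says which group is subtracted from which, gives an inequality to be met, restates the endpoint as freedom from anaemia, or mentions the upper limit.

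**The concern.** A non-inferiority conclusion needs three things to agree: the direction of the difference, the sign of the margin, and the confidence limit that is compared with it. The protocol fixes only the limit.

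Section 11.1 names the comparison as "demonstrating non-inferiority of ACT + SLDPQ compared to ACT alone". Read as test minus control, excess anaemia on SLDPQ gives a positive difference. Harm beyond the margin is excluded only when the upper limit lies below +2.5 points. The lower limit shows how small the excess might be, not how large, so it cannot support a claim of no unacceptable excess.

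Lower-limit wording is normal for an efficacy endpoint such as a cure rate, where higher is better, and it may have been carried over from one. What is at stake is the decision rule for the primary question, whether SLDPQ is acceptably safe in G6PDd children, in a trial meant to inform drug policy.

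**Working it through.** **Inputs.** From section 11.1: control rate 1.5%, margin 2.5 points, two-sided alpha 0.05 (2.5% in the relevant tail), power 80%, 374 per group, 800 G6PDd children in all. Assumptions: equal true rates for the sample size; a 1:1 SLDPQ:placebo split, hence 800/2 = 400 per group; true SLDPQ rates from 1.5% to 10% for the error rates; Wald limits, since section 11.2 names no interval method.

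**Step 1: the plan's own sample size.** n = (z₀.₉₇₅ + z₀.₈₀)² × [p₁(1 − p₁) + p₀(1 − p₀)] / margin². With p₁ = p₀ = 0.015:

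- z values rounded to 1.96 and 0.84: 7.84 × (2 × 0.015 × 0.985) / 0.025² = 370.7
- unrounded z values: 372 after rounding up
- (z₀.₉₇₅ + z₀.₈₀)² rounded to 7.9: 373.5, that is 374

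The stated 374 is reproduced as an ordinary non-inferiority calculation. At equal rates it does not reveal which limit was meant, because the two directions are then symmetric.

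**Step 2: when the lower limit is right.** Let T be the SLDPQ proportion and C the control proportion. The lower limit of C − T is minus the upper limit of T − C. So the rule that the lower limit of C − T exceeds −2.5 is identical to the rule that the upper limit of T − C is below +2.5. Taking the proportion free of anaemia reverses the sign in the same way. Without one of these reversals the lower limit is the wrong one.

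**Step 3: error rates if the difference is T − C.** Exact binomial enumeration, 374 per group, control rate 1.5%. Entries are the probability of declaring non-inferiority.

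| True SLDPQ rate | True excess (points) | Lower limit > −2.5 | Lower limit < +2.5 | Upper limit < +2.5 |
|---|---|---|---|---|
| 1.5% | 0 | 79.8% | 100.0% | 79.8% |
| 3.0% | 1.5 | 96.4% | 99.9% | 17.6% |
| 4.0% (at the margin) | 2.5 | 99.1% | 98.1% | 3.4% |
| 5.0% | 3.5 | 99.8% | 89.8% | 0.5% |
| 6.5% | 5.0 | 99.99% | 58.6% | 0.02% |
| 8.0% | 6.5 | 100.0% | 24.0% | 0.0% |
| 10.0% | 8.5 | 100.0% | 3.6% | 0.0% |

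With 400 per group the pattern is the same. At 4.0% the three rules give 99.4%, 98.2% and 3.3%, and at equal rates the upper-limit rule gives 81.5%. The 3.4% is a little above the nominal 2.5%, reflecting the approximate Wald interval with few events; the choice of interval is a separate matter.

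**Step 4: two possible results, 400 per group, T − C.**

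- 26 v 6 events: 6.5% − 1.5% = 5.0 points; standard error √[(0.065 × 0.935 + 0.015 × 0.985)/400] = 0.01374; 95% CI 5.0 ± 1.96 × 1.374 = 2.31 to 7.69. Both lower-limit readings pass and the upper-limit rule fails.
- 12 v 6 events: difference 1.5 points, 95% CI −0.55 to 3.55. Again both lower-limit readings pass and the upper-limit rule fails. Here the interval includes zero.

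Taking C − T instead, the lower limits are −7.69 and −3.55. Both fall beyond −2.5, so both results correctly fail.

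**The case against.** The strongest reply is that the protocol never writes the subtraction order. To say that one treatment is compared with another is ordinary English and does not define test minus control. If control minus test was intended, the lower limit against −2.5 is correct. This stands, and it limits the point: the protocol is ambiguous on direction, and the named limit is wrong under the usual convention. A reader might infer that a clearly harmful regimen would be declared non-inferior in this trial. The documents do not support that, because they state no direction, sign or inequality, and every error rate above depends on the reading chosen.

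The two lower-limit readings also differ. Under *lower limit > −2.5*, the usual form of a lower-limit rule, the pass rate rises with harm. Under *lower limit < +2.5*, which the text does not state either, large harm would usually still be rejected: 3.6% pass at 10% v 1.5%.

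Second, section 11.2 also plans a two-sided chi-squared or Fisher test at 0.05, and the full interval would be calculated, so gross harm would be seen. For 26 v 6 in 400 per group, z = 0.05/√(2 × 0.04 × 0.96/400) = 3.61, p about 0.0003. That tempers the risk but does not supply a decision rule. With 12 v 6 the interval includes zero, so the difference test offers no warning, while the lower-limit rule still passes a result that has not excluded the margin.

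Third, section 11.2 calls itself a summary and defers detail to a later analysis plan, which may settle the direction. But the protocol does name a limit. An analysis plan that silently used the other one would contradict it.

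A reader might also infer that the reference to the whole data set brings G6PD-normal children into the non-inferiority test. It does not: the same sentence explains the phrase as both sites combined, and section 11.2 has already placed the test in the G6PDd group.

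**Conclusion.** The point holds in this form. The protocol decides non-inferiority for a harmful outcome on the lower confidence limit and defines neither the direction of the difference nor the sign of the margin. Under the conventional difference, that limit cannot exclude excess harm. Nothing in the protocol reverses the subtraction or recasts the endpoint.

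Conditional on the conventional difference, a 1.5% control rate, 374 per group and Wald limits, a true excess exactly at the margin would be declared non-inferior about 98% or 99% of the time, depending on the inequality, against about 3.4% under the upper-limit rule. If the reversed difference was meant, the intended rule is already correct and only the wording is incomplete.

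The sample size, margin and alpha are unaffected. Because the sentence governs the primary conclusion, it should be corrected before unblinding.

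**What to change.** In section 11.2, replace the phrase that names the lower end of the interval with: *Non-inferiority is concluded if the upper limit of the two-sided 95% CI for the risk difference (ACT + SLDPQ minus ACT + placebo) in the G6PDd group, both sites combined, is below +2.5 percentage points.* Carry the same sentence into the analysis plan. If the sponsor prefers control minus test, the equivalent is to state that order and require the lower limit to exceed −2.5 points. No separate change to the whole-data-set wording is needed.

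The cost is one sentence in each document. No extra patients or data are required, and power at equal rates remains about 80% with 374 per group.
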